### Schedule of activities

The Schedule of Activities table provides an overview of the protocol visits and procedures. Refer to Clinical Procedures for detailed information on each procedure and assessment required for compliance with the protocol.

### Schedule of Activities

| Protocol Activity                                | D0 (can be up to 2 weeks before D1) | Interim Visit (at least 5 days before surgery appointment) | D1 | D2 | D3-8 | D8 | D31 | After 2 months | After all patients |
|--------------------------------------------------|-------------------------------------|------------------------------------------------------------|----|----|------|----|-----|----------------|--------------------|
| Signature of informed consent form               | X                                   |                                                            |    |    |      |    |     |                |                    |
| Verification of inclusion and exclusion criteria | X                                   |                                                            |    |    |      |    |     |                |                    |
| Demographics                                     | X                                   |                                                            |    |    |      |    |     |                |                    |
| Outpatient recovery protocol in hospital         |                                     |                                                            | X  |    |      |    |     |                |                    |
| Regular recovery protocol in hospital            |                                     |                                                            | X  | X  |      |    |     |                |                    |
| Teleconsultation for outpatient recovery group   |                                     |                                                            |    | X  |      |    |     |                |                    |
| Telemonitoring for outpatient recovery group     |                                     |                                                            |    | X  | X    |    |     |                |                    |

|                                                            |   |  |   |   |   |   |   |   |   |
|------------------------------------------------------------|---|--|---|---|---|---|---|---|---|
| Patient calls to hospital in case of pain or concern       |   |  |   | X | X |   |   |   |   |
| Patient removes Healthdot. Patient fills in questionnaire. |   |  |   |   |   | X |   |   |   |
| End of study                                               |   |  |   |   |   | X |   |   |   |
| Interview about dashboard with Healthcare professionals    |   |  |   |   |   |   |   | X |   |
| Healthcare professionals fill in questionnaire             |   |  |   |   |   |   |   |   | X |
| CRF completion, including 30-day readmission               |   |  |   |   |   |   | X |   |   |
| Adverse event documentation                                | X |  | X | X | X | X |   |   |   |
| Device accountability logging                              |   |  | X |   |   | X |   |   |   |

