## 6 CLINICAL INVESTIGATION DESIGN

### 6.1 General

This clinical investigation is designed as a single center patient preference trial in a tertiary hospital in the Netherlands. We will test for non-inferiority of the outcome of the outpatient recovery after standard bariatric surgery compared to the current treatment, as well as evaluate the feasibility of the outpatient recovery after standard bariatric surgery.

To avoid bias, patient preference for either the current recovery path (group B) or the outpatient recovery (group A) after standard bariatric surgery is noted to be able to include the preference factor in the analysis. The patients that don't have a preference will be randomly assigned. The number of patients included in each group will be equal.

The primary endpoint of the study is the combined outcome measure, based on the following:

- Mortality
- Severe postoperative complications (Clavien-Dindo IIIb or higher)
- Readmission (at least one night in hospital)
- Mild complications (Clavien-Dindo II and IIIa)
- Prolonged length of stay (3 days or more in hospital)

within 30 days after primary surgery.

The secondary endpoints of the study are:

- Patient satisfaction >6 points (on a scale of 1-10)
- Percentage of patients recruited for the outpatient recovery after standard bariatric surgery group
- Percentage of patients with full adherence to protocol and randomization
- Percentage of missing data

|                                                                                                                    |              |                        |                  |                    |
|--------------------------------------------------------------------------------------------------------------------|--------------|------------------------|------------------|--------------------|
| Title: Clinical Investigation Plan                                                                                 |              | Author: [name] |                  | Philips restricted |
| DocID: ICBE-2-36455                                                                                                | Version: 3.0 | Date: 2020-DEC-08      | Status: Approved | Page: 22 of 44     |
| This document is based on Philips Research Template: Clinical Investigation Plan, ID: QR-TEM-57, Date: 2019-Mar-21 |              |                        |                  |                    |

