For each patient, the parameters mortality, severe postoperative complications (Clavien-Dindo IIIb or higher), readmission (at least one night in hospital), mild complications (Clavien-Dindo II and IIIa) and prolonged length of stay (3 days or more in hospital) within 30 days after primary surgery will be determined from the patient medical record by the principal investigator. Patient satisfaction will be obtained through a questionnaire at the end of the 8-day study period. Healthcare professional satisfaction will be obtained through questionnaires after all patients have completed the study. Percentage of missing data will be determined at the end of the study. False positive and false negative notifications from the Healthdot system will be noted by the healthcare professional that receives the notifications. Clinical decisions made based on the Healthdot system, that changed when information from a telephone consultation was also included, will be noted by the healthcare professional that makes the decisions. The costs will be estimated for each patient, based on the events that occurred as noted in the patient medical file. The principal investigator will retrieve this information from the patient medical file. Costs calculation will include hospital stay, additional contacts, re-admission-hospital stay for mild complications (less than Clavien Dindo 3, like superficial woundinfection, dehydration, pain or worryiness patient).

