#### **Enrollment schedule**

The point of enrollment is the time at which, following recruitment, a subject signs and dates the informed consent form. The first subject is expected to be enrolled in September 2020. The Clinical Investigation is expected to take 8 months. The duration of the active participation of each subject is 8 days.

In this clinical investigation, 200 patients will be enrolled. The enrolment period will be 6-7 months. Half of the patients will be assigned to the outpatient group, and half of the patients will be assigned to the regular treatment group. Patients included in the study can choose in which group they want to be. This way they can choose whether they receive outpatient recovery or the regular treatment. If the preferred group is full, the patient can choose to participate in the other group, or to withdraw from the study. If the patient has no preference, he/she is randomly assigned to either treatment, or if one group is full, to the treatment for which 100 patients have not yet been included. Patient preference is recorded.

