| - Start with sips of water, expanding to clear liquids                                                                                                                                                                                                                                                                                                                                                                                  | - Start with sips of water, expanding to clear liquids                                                                                                                                                                                                                                                                                                                                                                                  |                                                                                                                                                                                                                                         |
| 
By nurse, between 16:00h and 17:00h:
 
 
- Check Early Warning Score (EWS) and pain score
 
- Inspecting the wound
 
- Ensure micturition within 6 hours after surgery
 
- Explain and instruct patient about fragmin (blood thinner) injections (to be used for 4 weeks)
 
- Explain postoperative lifestyle/nutritional advice/upcoming appointments
 
 |                                                                                                                                                                                                                                                                                                                                                                                                                                         | The activities that occur at this point in the patients leaving on the same day is part of the standard of care but performed earlier that day. This will also happen later in the regular recovery group.                              |

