### Termination of entire study on statistical grounds

Based on the interim analysis, the study could be stopped in case of unacceptable inferiority or unanticipated accumulation of adverse events increasing patient risks to an unacceptable level.

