### Foreseeable adverse events and anticipated adverse device effects

No anticipated adverse device effects have been identified. However, since the study described here aims at detecting deterioration of health in patients post surgery, the following adverse events not associated with this study but with surgery in general are expected:

- Bleeding
- Anemia
- Anastomotic leakage
- Infection: wound, abdominal, pneumonia, urinary tract
- Dehydration
- Delayed gastric emptying
- Thrombosis: cerebral or cardiac infarction, intestinal ischemia, lung embolism

According to the Inspectie voor de Gezondheidszorg (Aanmeldingsformulier klinisch onderzoek met medisch hulpmiddel, Bijlage E 2017-07-14) these adverse events even if considered serious are not reportable since they are expected and described here as long as they do not lead to the suspension or termination of the trial or result in a change of the investigational product.

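### The Schedule of Activities stops adverse-event documentation at day 8, so the adverse-event comparison covers about one week of a 30-day endpoint window

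*Protocol*

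**What the plan says.** The Schedule of Activities (section 6.4) has a row "Adverse event documentation" with marks under D0, D1, D2, D3-8 and D8, and none under D31. The end-of-study row is marked only at D8. The one patient-level activity after D8 is "CRF completion, including 30-day readmission", at D31. The Enrollment schedule in section 6.3 agrees with the short window: "The duration of the active participation of each subject is 8 days".

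The primary endpoint in section 6.1 combines mortality, severe and mild complications (Clavien-Dindo II and above), readmission and prolonged stay, all "within 30 days after primary surgery". Section 6.1 adds that these items "will be determined from the patient medical record by the principal investigator".

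The number of adverse events in each group is a secondary objective, a secondary hypothesis (section 5) and a secondary endpoint (section 6.1). None of the three gives a time window. Section 14 (Reportability) requires all adverse events to go to the Study Manager, also without an end date.

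Two further places matter. Section 7 allows the study to be stopped, on the basis of the interim analysis, for inferiority or for "unanticipated accumulation of adverse events increasing patient risks to an unacceptable level". Section 14 (Foreseeable adverse events) lists expected surgical complications, among them anastomotic leakage and "Thrombosis: cerebral or cardiac infarction, intestinal ischemia, lung embolism". It declares them not reportable even if serious, unless they lead to suspension or termination of the trial or to a change of the product.

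**The concern.** The protocol uses two follow-up lengths without saying that it means to. The endpoint that decides the trial runs for 30 days. The only period stated for recording harms ends at D8, when the subject is also said to have left the study.

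The two sets of events overlap by the protocol's own definitions. Section 14 defines a serious adverse event to include one that led to death, or to serious deterioration resulting in hospital admission. A death, or a readmission for serious deterioration, between D9 and D31 is therefore both a primary-endpoint failure and a serious adverse event. A site that follows the schedule would record only the first.

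At stake is the safety comparison in a trial meant to show that same-day discharge adds no risk. The report could show a late death or readmission in the primary result and no matching entry in the adverse-event table. Events below Clavien-Dindo II after D8, unless they lead to an overnight readmission, have no planned place of collection.

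**Working it through.** The protocol gives no figure to reproduce here. The check is a reading of the schedule by column, then a count of days.

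**Inputs**
- Surgery is on day 1 (Table 1), so D1 is postoperative day 0, D8 is postoperative day 7 and D31 is postoperative day 30. The D31 column fits this numbering.
- Last mark for adverse-event documentation: D8 (Schedule of Activities).
- Primary-endpoint window: 30 days after surgery (sections 5, 6.1 and 7).
- Adverse-event period in section 14: none stated.
- Adverse-event window for the secondary endpoint: none stated.

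**Is the schedule really the only window?** The text above it calls it an overview and sends the reader to Clinical Procedures for detail. That section describes the hospital stay, discharge, the D2 teleconsultation, D3-8 monitoring, the D8 questionnaire and the 30-day check of readmission from the record. It sets no adverse-event period. Section 14 sets none either. Nothing elsewhere replaces the D8 limit.

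**Days outside the window**
- Postoperative days not covered: 30 − 7 = 23.
- Share: 23 / 30 = 0.767, or 77%.

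**Where an event falls**

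| Event | Primary endpoint | Adverse-event count under the schedule |
|---|---|---|
| Death, Clavien-Dindo II or higher, or overnight readmission, up to D8 | counted | counted |
| The same, D9-D31 | counted, by chart review | not scheduled |
| Below Clavien-Dindo II without overnight readmission, up to D8 | not counted | counted |
| The same, D9-D31 | not counted | not scheduled |

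The cost endpoint does not fill the last row, because it covers only 7 days after surgery.

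**How many endpoint events could be affected.** Section 7 states that 95% of current patients have none of the events, and the sample-size paragraph uses 0.96. Over 200 patients this gives 200 × 0.05 = 10 or 200 × 0.04 = 8 composite failures. The protocol does not say what share arises after D8, so that share is an assumption. At 10% it is about 1 event (0.8 to 1.0); at 50% it is 4 to 5. The numbers are small, but the composite holds the gravest events in the trial.

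**Possible delay.** If a site logged nothing after D8, an event on D9 would first surface at the D31 form: 31 − 9 = 22 days. This is a worst case.

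**After the change.** With the row extended to D31, all 30 postoperative days are covered instead of 7. The sample size does not change.

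**The case against.** The strongest reply is that little of importance is lost. The principal investigator takes death, complications of Clavien-Dindo II or higher and readmission to 30 days from the record for every patient. The interim analysis compares this same outcome, and 30-day readmission separately. This stands, and it limits the point to the adverse-event records and lesser late events. A reader might infer that the stopping decision cannot see anything after D8. That is not so: the inferiority part of the rule uses 30-day data, and only the part on accumulating adverse events has the shorter view.

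A reader might also infer that a late serious event is never recorded as such and misses a 24-hour deadline. The document does not say this. Section 14 has no day-8 cut-off, so the gap is an inference from blank cells. In the text of the timelines table, the 24-hour line to the Study Manager is printed on the adverse-device-effect row, and the serious-adverse-event cell is empty, probably because cells were merged. For leakage, lung embolism and the other listed complications, section 14 separately removes reportability. That exemption cites the inspectorate and may leave the duty to the Study Manager intact, but any loss of authority reporting for those events does not come from the D8 stop alone. Delayed reporting is therefore a possible consequence, not a rule of the plan.

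The four-week blood-thinner course might seem to strengthen the case. It adds nothing: it is standard care, and both groups receive the same instruction. The list of expected complications also gives no timing, so the 30-day horizon rests on the endpoint definition.

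Finally, a harm window matched to device wear could be a deliberate choice, and being equal in both groups it does not by itself bias the comparison. But the protocol never states that choice, and section 14's open-ended duty points the other way. The strategy under test is early discharge, whose outcome the protocol itself judges at 30 days.

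**Conclusion.** The point holds as an inconsistency between the schedule, section 14 and the endpoint window. By the only window stated, 23 of 30 postoperative days (77%) have no scheduled adverse-event documentation, and the secondary adverse-event endpoint becomes an 8-day count beside a 30-day primary endpoint. A death, or a readmission that meets the serious-adverse-event definition, on D9-D31 can appear in one and not the other. Lesser events in that period appear in neither.

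This rests on two assumptions: that sites follow the schedule as printed, and that D1 is the day of surgery. The primary comparison, its sample size and the 30-day interim comparison are not affected. The documents do not support saying that late serious events are lost to the trial, or that the plan permits late reporting of them.

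**What to change.** - In the Schedule of Activities, extend the adverse-event row to D31 for both groups and move the end-of-study mark from D8 to D31. Device wear still ends at D8. Align the wording on 8 days of active participation.
- In section 14, state that adverse-event reporting applies through D31 and that each timeline starts when the site becomes aware of the event. Chart review at D31 cannot by itself secure prompt reporting, so this sentence is needed as well as the longer row.
- Reconcile that sentence with the paragraph on listed complications: say whether the exemption covers only reports to authorities or also the report to the Study Manager.
- In sections 5 and 6.1, define the secondary endpoint as adverse events within 30 days after surgery.
- At the D31 review already planned, enter complications found in the chart as adverse events or serious adverse events, so that the two datasets can be checked against each other.

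The cost is an amendment to two table rows and a few sentences, more adverse-event forms, and formal participation that is 31 − 8 = 23 days longer. No visit or procedure is added.

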### Sponsor activities

The sponsor will provide the Healthdot system, and instruct the investigators on how to handle the Healthdot device, where to position it, and how to use the system. The Sponsor will provide the infrastructure to view the transmitted signals on the dashboard inside the hospital.

## 6.5 Monitoring plan

- ☐ Study does not require on-site monitoring. Justify here (e.g., non WMO study in NL); consult with Q&R Manager as needed:

The monitoring plan to be followed, including access to source data and the extent of source data verification planned, is described in a separate document.

## 7 STATISTICAL CONSIDERATIONS

### Study population

All patients who are randomized will be included into the analysis and analyzed according to the group they were originally assigned to, regardless of what treatment (if any) they received (intention to treat analysis).

|                                                                                                                    |              |                         |                  |                    |
|--------------------------------------------------------------------------------------------------------------------|--------------|-------------------------|------------------|--------------------|
| Title: Clinical Investigation Plan                                                                                 |              | Author: [name] |                  | Philips restricted |
| DocID: ICBE-2-36455                                                                                                | Version: 3.0 | Date: 2020-DEC-08       | Status: Approved | Page: 32 of 44     |
| This document is based on Philips Research Template: Clinical Investigation Plan, ID: QR-TEM-57, Date: 2019-Mar-21 |              |                         |                  |                    |

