### Clinical procedures

#### *Patient screening/inclusion*

The patients are recruited during the pre-operative consultation at the obesity centre. Patients are informed about the study and will be asked if they are interested in participating in a study in which they could either receive regular treatment (stay at least one night in hospital) or undergo standard f care surgery and leave the hospital on the same day while being monitored with use of the Healthdot. Interested patients are handed out the information letter including the informed consent form. If the patient agrees to participate and signs informed consent he/she can be enrolled into the study. The patient can choose whether he/she wants to be assigned to outpatient recovery or the regular recovery path. If the preferred group is full, the patient can choose to participate in the other group, or to withdraw from the study. If the patient has no preference, he/she is randomly assigned to either recovery path. Randomization is done by computer software. However, if one group is already full, the patient will be assigned to the group for which 100 patients have not yet been included. Patient preference is recorded. As demographics the following data of the patient are collected: Age, height, weight, gender.

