#### *Start of the study*

The activities in both groups are outlined in

[Table 1](#)

[Table 1](#), with the differences between the two groups described for clarity. Patients who have chosen to undergo outpatient recovery will be scheduled for surgery on the earliest available time-slots (before 12:00). The Healthdot will be applied mid-clavicular on the lowest left rib of the chest after surgery. HealthdotThe Healthdot can be removed by the patient themselves in case of emergency with a remover tissue which will be handed out to the patient before discharge. The patient will be instructed on how to remove the Healthdot with the tissue. The postoperative standard care will be arranged in such a way that same day discharge is possible for this group of patients. Patients who have chosen the regular recovery path will receive care in accordance with current protocol.

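### The analysis set is limited to randomised patients although every patient may choose a group, and the only primary test named would compare the pooled, partly self-selected groups without adjustment

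*Protocol*

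**What the plan says.** Four parts of the protocol bear on this.

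- **Analysis set** (Section 7, Study population): "All patients who are randomized will be included into the analysis and analyzed according to the group they were originally assigned to". This is labelled intention to treat.
- **Allocation** (Section 6.3, Enrollment schedule; repeated in the Executive Summary and in Section 6.4, Patient screening/inclusion): "Patients included in the study can choose in which group they want to be". Section 6.1 adds "The patients that don't have a preference will be randomly assigned". When one group is complete, a patient without a preference goes "to the treatment for which 100 patients have not yet been included". For patients who do have a preference, "If the preferred group is full, the patient can choose to participate in the other group, or to withdraw from the study".
- **Size and test** (Section 7, Sample size and Statistical design): 97 patients per group, rounded up to 100, tested with an uncorrected chi-squared statistic against a 7% margin. No stratification or adjustment is named.
- **Use of preference**: Section 6.1 says that preference, as a guard against bias, "is noted to be able to include the preference factor in the analysis". The Executive Summary (Investigation procedures) also says that it will be analysed. Section 7 contains no such analysis. The one defined use is a secondary comparison, within the Healthdot group, of patients who chose it with patients randomised to it.

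**The concern.** The stated analysis set belongs to a fully randomised trial, and this is a preference trial. Read as written, the set drops everyone who chose a group and everyone placed because the other group was full, while the sample size counts them all. Read as the rest of the protocol implies, with all 200 pooled, the number is right but the contrast is not randomised, and the named test does nothing about that.

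The primary comparison decides whether the study counts as successful (Section 7, Pass/fail criteria), and claims may be derived from it (Section 5). Baseline differences between the groups could therefore produce a false non-inferiority conclusion or hide a true one. Leaving the set open also lets it be settled after the data are seen.

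**Working it through.** **1. The plan's own number.** Inputs from Section 7, Sample size: proportion 0.96 in both groups, margin 0.07, power 0.80, alpha 0.05. Sidedness is not stated. One-sided 5% reproduces the figure:

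n = (1.645 + 0.842)² × 2 × 0.96 × 0.04 / 0.07² = 6.183 × 0.0768 / 0.0049 = 96.9, so 97 per group.

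One-sided 2.5% would give 124. The 97 therefore needs 194 patients in the comparison, which is 97% of the 200 enrolled.

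**2. Literal reading: randomised patients only.** Power = Φ(0.07 / √(0.0768/n) − 1.645), with n randomised per group and an even split. The share without a preference is not in the protocol, so the rows are assumptions.

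| Randomised of 200 | n per group | Power at 0.96 |
|---|---|---|
| 200 | 100 | 81% |
| 150 | 75 | 71% |
| 100 | 50 | 56% |
| 80 | 40 | 48% |
| 40 | 20 | 30% |

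Worked row, n = 50: √(0.0768/50) = 0.0392; 0.07/0.0392 = 1.786; Φ(0.141) = 56%. In the last row only 20 × 0.04 = 0.8 failures are expected per group, so the normal approximation is rough there.

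**3. Pooled reading: who ends up where.**

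| Preference | Group received |
|---|---|
| Outpatient | Outpatient, or regular (or withdrawal) if outpatient is full |
| Regular | Regular, or outpatient (or withdrawal) if regular is full |
| None | Random while both are open, otherwise the open group |

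Leaving aside replacement of early dropouts, recruitment continues only while at least one group is open, so overflow can run in one direction only. At least one preference stratum then contains a single group. A model with terms for preference and group would learn about the group effect only from the no-preference patients and the late overflow. Preference alone therefore cannot remove the confounding while keeping the information of 200 patients.

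**4. What a selection effect would do to the crude test.** The protocol gives neither its size nor its direction, so 2 points each way is an assumption. With 100 per group and 0.96 in the regular group:

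- *Advantage to outpatients, true deficit at the margin (0.89).* The observed outpatient rate is 0.91. SE = √((0.0384 + 0.0819)/100) = 0.0347. P(non-inferiority) = Φ(0.02/0.0347 − 1.645) = Φ(−1.068) = 14%, against 5% without bias. One point gives 9%; three points give 23%.
- *Disadvantage to outpatients, true rates equal.* The observed outpatient rate is 0.94. SE = √((0.0384 + 0.0564)/100) = 0.0308. Power = Φ(0.05/0.0308 − 1.645) = Φ(−0.021) = 49%, against 81% without bias.

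**The case against.** The fairest reply is that the literal reading is strained. Sections 6.1, 6.3 and 7 all count 200 patients in equal groups, and the protocol says assigned for patients who choose as well. Stock intention-to-treat wording is the likely source. That is probably right, and it means the low powers in step 2 show what the sentence implies, not what is likely to be done. The sentence still defines the primary set, and no separate analysis plan could reconcile it with 100 per group.

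A second reply is that preference is not ignored: two places say it will be used, and how it enters a model may be left to an analysis plan that is not at hand. This stands in part. The criticism is of the primary test that Section 7 does name, which is unadjusted, and of its mismatch with those two statements. Self-selection itself is an openly declared feature of the design and is not an error.

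A reader might go further in three ways that the protocol does not support:

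- *That fitter patients will choose same-day discharge, so the bias must favour non-inferiority.* Nothing in the document shows who will choose which group.
- *That dilution from outpatients kept overnight can be sized from the adherence threshold of more than 75%.* That is a feasibility threshold for adherence to the protocol as a whole. It is neither a same-day discharge rate nor an expected value.
- *That a per-protocol set of patients discharged on the planned day would be a safeguard.* Discharge depends on the postoperative course, and a stay of 3 days or more is an endpoint component. Such a set would remove events by construction and could favour non-inferiority.

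**Conclusion.** The analysis set is wrong as written. It contradicts the allocation scheme and the sample size, and this conclusion needs no assumption. Read literally, the comparison falls below 80% power unless about 97% of patients are randomised; how far below depends on a share that the protocol does not give.

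Under the pooled reading the number is sufficient, but the groups are self-selected to the extent that patients have a preference. Section 7 does not carry out the use of preference announced elsewhere, and a preference term alone could not do the job. The error rates in step 4 (14% false non-inferiority, or 49% power) illustrate an assumed 2-point bias. They are not estimates, and the protocol does not say which way a bias would run. It would therefore go too far to conclude that the trial is far too small or that its result will be biased toward non-inferiority.

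**What to change.** 1. Define the primary set as all patients assigned to a group, whether by choice, by computer, or because the other group was full, analysed in that group. Record the allocation route for each patient.
2. Make the primary estimate a parsimonious baseline-adjusted risk difference judged against 7%, with the crude estimate beside it. Standardisation or propensity weighting on age, sex and BMI is feasible, since Section 6.4 states "As demographics the following data of the patient are collected: Age, height, weight, gender". Add procedure (sleeve or bypass) if it is captured. State that residual confounding remains, because no comorbidity is on that list.
3. Report separately, with a confidence interval, the patients randomised by computer while both groups were open.
4. Optionally, add a sensitivity analysis limited to regular patients operated before 12:00. Outpatient surgery is confined to the morning and Table 1 sets no such limit for the regular group. The protocol does not show that timing affects the 30-day outcome, so this is a check only.

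**Cost.** No extra patients or visits are needed. Sections 6 and 7 are protocol text, so the change needs an amendment under Section 9. Events will be few (200 × 5% = 10 at the site's current 95%), so the model must stay small and the interval may widen slightly. Procedure and surgery time are not among the listed baseline data and would have to be captured.
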